### Secondary outcome measures

4.2

We will use mean blood glucose (MBG), largest amplitude of glycemic excursions (LAGE), postprandial glycemic excursions (PPGE), glycated hemoglobin as the secondary outcome measures. In the whole process, we will also collect the following indicators:

(1)Total effective rate; the judgement of effectiveness takes into account the improvement of examination indicators and the relief of clinical symptoms.(2)Hyperglycemia or hypoglycemia that may occur during the study.(3)Have any adverse effects of medication throughout the process.

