### Randomization and blinding

2.6

A software called SPSS Statistics Version 17.0 (IBM Corp., Armonk, New York) will be used to generate randomization sequence. The randomization sequence will be concealed and disseminated using opaque envelopes. Participants will be randomly divided into an intervention group and a control group in this way. In the progress of our study, evaluators, participants, and experimental researchers will be blinded. Unblinding is allowed to be performed only when the participant has an adverse reaction. The first time an adverse reaction occurs, the principal investigator will immediately assess the patient's condition and record in detail the time, place, and possible cause of the adverse reaction in Case Report Forms. In this experiment, the drug distribution managers and data analysis experts will not be directly involved in the process of the study and intentional analysis will be applied to the unblinding participants.

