### Monitoring

4.6

According to recommendation of the National Institutes of Health (NIH), this trial established an independent Data and Safety Monitoring Board (DSMB). The committee consists of 3 members, including a Chinese medicine clinician, an endocrinologist, and a statistician. The committee will supervises whether the study follows the protocol design and standard guidelines, will monitor the progress of the trial, and will observe whether adverse events and etiologies are adequately recorded. This DSMB also identify problems in the project, if any; the committee will make the decisions to change the details of this protocol and announce the research personnel by written notice after approval by the ethics committee. Moreover, a qualified clinical trial expert will be invited to monitor this trial and the will take full responsibility and make the final decision.

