## Discussion

5

Elderly patients with type 2 diabetes are more prone to hypoglycemia and blood glucose variation. In terms of physiology, with increasing age, the plasma albumin concentration of the elderly gradually decreases, and the drug–protein binding rate decreases, resulting in an increase in free drug concentration and an increase in the effect of the drug. At the same time, the decrease in liver blood flow and the number of functional hepatocytes and the decrease in the activity of liver microsomal enzymes have led to a decline in the liver's ability to metabolize drugs in the elderly and a prolonged plasma half-life. Renal function declines with age, glomerular filtration rate decreases, renal blood flow decreases significantly, and renal tubular function declines. These changes easily make the elderly more likely to cause hypoglycemic reactions when using conventional doses of hypoglycemic drugs, thus making the elderly more variable in blood glucose.^[29,30]^ In terms of pathology, with the progress of the disease, decreased islet function reduces the ability to regulate blood sugar. The vulnerability of the elderly to oxidative stress, inflammatory factors, and endothelial dysfunction makes the islet resistance even worse. Under the influence of these factors, the variability of blood sugar increases, making the risk of diabetes complications in elderly patients increased. Glycemic variability is positively associated with micro- and macrovascular complications, which have more deleterious effects than sustained hyperglycemia in the pathogenesis of diabetic cardiovascular complications. Glycemic variability causes vascular injury by increasing oxidative stress and endothelial dysfunction, and exacerbating chronic inflammatory state.^[31,32]^ What can we do to reduce the variability of blood glucose in elderly patients with type 2 diabetes and find an effectual and acceptable method has become one of the increasing concerns in the medical field. TCM has the advantages of safe use, less adverse reactions, and side effects, in addition, it also has a mature overall concept and a large number of clinical experience summary. From the perspective of dialectical holistic view, traditional Chinese medicine regulates the balance of yin and yang in the human body, and has unique advantages such as flexible composition compatibility and personalized dialectical treatment. Chinese medicine has accumulated in long-term clinical practice, a wealth of experience in the diagnosis and treatment, but this is a subjective evaluation, is considered to be low-quality evidence based medicine. Therefore, it is important to conduct well-designed clinical studies to provide high-quality EBM evidence. The test is valuable because it can provide scientific evidence and rigorous EBM efficacy and safety about SC on glycemic variability of type 2 diabetes in the elderly.

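### The general safety item counts only effects attributed to medication, and cause need not be recorded before unblinding, so knowledge of the arm can influence the safety comparison

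*Protocol article*

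**What the plan says.** The Abstract says that the trial can provide evidence on the safety of SC as well as its efficacy. Section 4.2 (Secondary outcome measures) then lists two items that bear on safety. One is "Hyperglycemia or hypoglycemia that may occur during the study", which carries no condition on cause. The other is "Have any adverse effects of medication throughout the process", which does.

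Section 2.6 (Randomization and blinding) sets the handling: "Unblinding is allowed to be performed only when the participant has an adverse reaction". It continues: "The first time an adverse reaction occurs, the principal investigator will immediately assess the patient's condition", and the investigator is to "record in detail the time, place, and possible cause of the adverse reaction in Case Report Forms".

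Two later sections speak of adverse events. In section 4.4, under the item on allergic or serious reactions, the ethics committee assesses whether the event is related to the intervention. In section 4.6 (Monitoring), the monitoring board "will observe whether adverse events and etiologies are adequately recorded".

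**The concern.** Two features act together.

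First, an outcome defined as an effect of medication puts the causal judgement at the point of collection. A dizzy spell or a digestive complaint put down to age, diet or the disease itself would not qualify. An analysis plan cannot repair this later, because an event left off the form cannot be recovered.

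Second, the unblinding ground is the occurrence of any adverse reaction, with no reference to whether the allocation needs to be known. Section 3.2.1 already anticipates gastrointestinal discomfort with metformin, so a mild complaint of that kind could meet the condition. Nothing in section 2.6 fixes whether cause is recorded before or after the code is broken. A judgement of cause can therefore be made with the arm known.

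At stake is the safety comparison between arms. If the share of symptoms attributed to a drug differs by arm, equal true rates can look different, or a real difference can be hidden.

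**Working it through.** The point rests on wording. The protocol states no safety rate, safety power or safety sample size, so there is no figure of its own to reproduce.

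**The sections side by side**

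| Section | Term used | Is cause judged before or after recording? |
|---|---|---|
| 4.2, glucose item | hyper- or hypoglycemia | No attribution needed |
| 4.2, general item | adverse effects of medication | Before: attribution is part of the definition |
| 2.6 | adverse reaction | Mixed: the term is causal, yet a possible cause is still to be recorded |
| 4.4 | adverse event (allergic or serious reactions) | After: relation to the intervention is assessed by the ethics committee |
| 4.6 | adverse events and their etiologies | After: the board checks that both are recorded |

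The bodies in 4.4 and 4.6 need events recorded before attribution. The general item in 4.2 defines collection after it. The three terms are not reconciled.

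**What section 2.6 settles about unblinding**

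- Ground: any adverse reaction, with no limit by severity or by need to know the allocation.
- Who records cause: the principal investigator.
- Who opens the code: not stated.
- Order of recording cause and opening the code: not stated.

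**Illustration of size**

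Inputs: 30 participants per group (section 2.5), and a background rate of 7.6% for adverse reactions to hypoglycemic drugs (Introduction). The latter is not a planning value for this trial.

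- Expected reactions per arm: 30 × 0.076 = 2.28.
- Expected reactions over both arms: 60 × 0.076 = 4.56. Unblinding is permitted rather than required, so at this rate 4.56 is the expected number of participants eligible for a code break. It is not a forecast of code breaks.
- One reaction moved to a non-drug cause: 1 / 2.28 = 44% of an arm's expected count.

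Now let the true rate be equal in both arms and let the share attributed to medication differ. Expected recorded count per arm = 30 × rate × share. The shares of 80% and 50%, and the rates of 20% and 30%, are assumptions; the documents give none.

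| True rate in both arms | All-cause count per arm | Recorded at 80% share | Recorded at 50% share |
|---|---|---|---|
| 7.6% | 2.28 | 1.8 | 1.1 |
| 20% | 6.0 | 4.8 | 3.0 |
| 30% | 9.0 | 7.2 | 4.5 |

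The all-cause column does not depend on the shares and is the same in both arms. The recorded counts differ although nothing about safety does. Swapping the shares between arms reverses the direction.

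**The case against.** The strongest reply is that this is loose terminology in a condensed article. Section 2.6 has a possible cause recorded on the form, which suggests that a reaction need not already have been pinned on a drug. Section 2.6 also says that evaluators, participants and researchers are blinded. Section 4.4 gives the ethics committee a view on causality. Fields for severity or outcome, and the layout of the safety table, are commonly left to the full protocol and are no finding.

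Much of this stands, and it rules out several stronger readings that a reader might infer:

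- *That attributed reactions are all the trial collects.* The glucose item in 4.2 has no causal condition, and 4.6 expects adverse events to be recorded.
- *That repeat episodes, of hypoglycemia in particular, are lost.* The items in 4.2 are collected through the whole study. The reference in 2.6 to the first occurrence concerns how promptly the investigator responds, and may simply mean as soon as one occurs.
- *That the investigator who judges cause is the person who unblinds, and does so first.* The text says neither.
- *That the count will be biased towards SC.* The Discussion does say that "TCM has the advantages of safe use, less adverse reactions, and side effects", but this is a general remark and no rule for judging events. Metformin is given in both arms, so a symptom blamed on metformin would still count as an effect of medication. Only attribution to a non-drug cause removes it.

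The reply does not remove the core. The general item in 4.2 is worded causally, 4.4 and 4.6 assume otherwise, and 2.6 states an unblinding ground wider than need. The ethics committee's role sits in the item on allergic or serious reactions, so milder reactions have no stated second assessor.

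A tighter unblinding rule may also protect little. Sections 3.2.1 and 3.2.2 describe no placebo powder (the flowchart is not shown), and if there is none the arm may be apparent without any code break. That strengthens the case for all-cause recording, which depends least on anyone's judgement of cause.

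**Conclusion.** The point holds as a risk created by stated rules. Apart from hyper- and hypoglycemia, the safety outcome is defined by attribution to medication, in conflict with sections 4.4 and 4.6. Section 2.6 allows the code to be broken for any adverse reaction without requiring cause to be recorded first. The safety comparison can therefore be influenced by knowledge of the arm; the documents do not show that it is.

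Its size cannot be derived from the documents. The illustration shows only that counts per arm may be small enough for one or two judgements of cause to matter: 2.28 expected at the background rate, and 1.8 against 1.1 under the assumed attribution shares. The efficacy outcomes are not touched by this point. It should be corrected because the trial promises safety evidence and unrecorded events cannot be retrieved. Confidence is medium, since the looseness of terms leaves some doubt about what would be done in practice.

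**What to change.** 1. Reconcile sections 2.6, 4.2, 4.4 and 4.6 on one unit: every adverse event in both arms, recorded whatever its suspected cause. Compare all-cause events by arm as the main safety comparison.
2. Record relatedness as a separate field, entered by blinded assessors before any code break. The blinded evaluators already named in section 2.6 could do this.
3. In section 2.6, replace the occurrence of an adverse reaction as the ground for unblinding with a need to know the allocation. State who may break the code, and log each instance with its reason.

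The cost is protocol and case report form wording, with no added visits or staff. The small downside is that more minor events must be recorded, so reported event rates will be higher.

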### Efficacy evaluation

4.3

By calculating the SDBG and CV of the participants at baseline, the first month, the second month, and the third month, the efficacy will be evaluated (Table 2). At the same time, we will also evaluate MBG, LAGE, and PPGE, glycated hemoglobin as secondary efficacy evaluations. We will use a simple method is to get blood sugar and calculate the above indicators which is finger-prick measurements within a specific period, 7-point profiles (7 am, 9 am, 11 am, 1 pm, 5 pm, 7 pm, and 9 pm). Despite the lack of nocturnal blood glucose measurements, the SDBG can be an appropriate data even in data sets in which glucose values do not follow a Gaussian distribution, because it has a near linear relation with the interquartile range.^[27,28]^ In addition, we will measure the following indicators at baseline and at the end of the experiment: blood pressure, fasting plasma glucose, total cholesterol, low density lipoprotein cholesterol, high density lipoprotein cholesterol, triglycerides, advanced glycation end products, and changes in the scores of TCM syndromes measured by questionnaires.

**Table 2 T2:**
[figure not shown]
The calculation formulas.

### Conditions for suspension and withdrawal of clinical trials

4.4

The research staff of this clinical trial should record in detail the reasons why the participant proposed to withdraw from the clinical trial or the subjects’ reluctance to continue the clinical trial, and record in detail the evaluation indicators at the time of drug withdrawal. In addition, the reason for discontinuing the trial and its relationship with the clinical trial should be clearly documented. When the participants have the following conditions, we will suspend and withdraw clinical trials.

(1)People who quit the study themselves.(2)People who can’t insist on treatment.(3)In case of allergic reaction or serious adverse reaction during the test, the test shall be suspended. The ethics committee will assess any correlation between the adverse event and the intervention, and make a decision on whether the study should proceed.(4)Those who did not follow the plan strictly.(5)People who joined other clinical trials in the course of this experiment.

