### Sample size calculation

2.5

The study used SBDG and CV as the main outcome indicators. In the preliminary experiment, the mean value of SBDG between the 2 groups was 0.39, and the standard deviations of treatment group and control group were 0.28 and 0.35 respectively. On the other hand, the mean value of CV between the 2 groups was 0.41, and the standard deviations of treatment group and control group were 0.31 and 0.67 respectively. Set *α* to 0.05 and *β* to 0.1. The sample sizes calculated using PASS 11 software were 14 and 25, respectively. In order to ensure statistically meaningful results, considering the 20% dropout rate, and according to the formula of n ^ = n/(1–f), the total number of studies was determined to be 60 cases, 30 cases per group.

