#### Intervention group

3.2.2

Participants in this group will take the same dose of metformin as the control group. In addition, they will take SC. In this study, SC was provided by the Hospital of Chengdu University of traditional Chinese Medicine. The composition of the drug is: Ginseng, Rehmannia Glutinosa, Aspart Asparagus, Black Plum, Cinnamon, Coptis. The formula is made into powder according to the compatible dosage. Each dose is 88.5 g, divided into 3 parts, each part is taken with 200 mL of boiling water and taken 20 minutes before 3 meals. No other drugs are used during treatment period. It is worth mentioning that the change of conditions should be closely monitored at this time so as to control the deterioration of conditions in time.

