### Statistical analysis

4.5

Data processing uses SPSS statistical software version 17.0 (IBM Corporation). Normally distributed variables are expressed as mean and standard deviation; non-normally distributed variables are expressed as median and quartile range. Normally distributed variables between groups using independent sample *t* test, rather than the normal difference variables using Mann–Whitney *U* test. In the comparison group, paired *t* test variables were normally distributed, non-normally distributed variables the Wilcoxon rank sum test. *P* < .05 was considered a statistically significant difference. Study figures were created using SigmaPlot (Systat Software Inc.).

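### Non-adherence is a ground for withdrawal with no stated later follow-up, and analysis as randomised is mentioned only for unblinded participants, so the primary comparison risks resting on adherent participants

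*Protocol article*

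**What the plan says.** All references are to the protocol article.

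- **Section 4.4 (suspension and withdrawal).** The list is introduced by "When the participants have the following conditions, we will suspend and withdraw clinical trials". Two of its five grounds concern adherence after randomisation: "People who can’t insist on treatment" and "Those who did not follow the plan strictly". The second has no threshold, so any deviation could qualify. Staff are to "record in detail the evaluation indicators at the time of drug withdrawal". No later assessment is mentioned.
- **Section 2.6 (randomization and blinding).** The one sentence on analysis by assignment reads "intentional analysis will be applied to the unblinding participants". I take this to mean intention-to-treat.
- **Section 4 (outcome measures).** SDBG, CV and the secondary outcomes are due at baseline and at months 1, 2 and 3.
- **Section 4.5 (statistical analysis).** The between-group comparison is given as "Normally distributed variables between groups using independent sample *t* test", with Mann–Whitney otherwise. No rule for withdrawn participants is given.
- **Section 2.5 (sample size).** Thirty per group is reached "considering the 20% dropout rate", an overall rate that is not split by arm.
- **Section 3.2 (interventions).** Both arms take the same metformin. The SC arm also takes the powder: "Each dose is 88.5 g, divided into 3 parts, each part is taken with 200 mL of boiling water". No placebo powder is described for the control arm.

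**The concern.** Adherence is observed after randomisation and can depend on the assigned arm, on tolerance and on glycaemic response. If imperfect adherence ends participation, the later SDBG and CV values are missing for reasons that may be related to the outcome, and those who remain are no longer protected by the randomisation.

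Two features make this more than theoretical. The described regimens differ in burden, so a strict-adherence rule gives the SC arm more ways to fail. Section 3.2.2 also rules out other drugs during treatment. A participant given a further glucose-lowering drug could therefore be classed as a deviator, which would tie removal to the outcome itself.

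At stake is the primary comparison in a trial of 60. A later analysis plan can define who is analysed, but it cannot recover glucose profiles that were never taken.

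**Working it through.** **1. What the text fixes and what it leaves open.**

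| Question | Text | Result |
|---|---|---|
| Does non-adherence end participation? | 4.4 | Yes; no threshold |
| Is stopping treatment distinguished from leaving follow-up? | 4.4 | No |
| Which data are asked for on withdrawal? | 4.4 | Indicators when the drug is stopped; nothing later |
| Who is named for analysis as assigned? | 2.6 | Unblinded participants |
| Are withdrawn participants said to be left out of the analysis? | 4.4, 4.5 | Not stated |

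The loss of data after withdrawal follows from the text. Exclusion from the analysis does not; it is a risk. The named tests, as described, need a value at the visit compared. Someone without one drops out unless a further rule is given.

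**2. How many participants.** From section 2.5: 30 per arm and 20% dropout. 0.20 × 30 = 6 per arm, 12 of 60 in total, leaving 24 per arm. The article does not say what share of that 20% is adherence-related, so 6 per arm is a planning figure for all causes.

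On the plan's own figures, with two-sided α of 0.05 and 90% power, n per group = (s₁² + s₂²)(1.960 + 1.282)²/d². I read 0.39 and 0.41 as between-group differences.

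- SDBG: (0.28² + 0.35²) × 10.507/0.39² = 13.88, so 14, as stated.
- CV: (0.31² + 0.67²) × 10.507/0.41² = 34.07, so 35, against the stated 25.
- Inflation by the stated formula: 25/(1 − 0.2) = 31.25, so 32 per group, against the stated 30.

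The last two are separate matters and do not bear on the conclusion here.

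**3. Direction of bias.** Let f be the fraction of an arm removed, and d how much higher (worse) SDBG would be in those removed than in those retained. The full-arm mean is the retained mean plus f × d. The shift in favour of SC from analysing only retained participants is therefore

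shift = f(SC) × d(SC) − f(control) × d(control).

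Neither f by arm nor d is in the article. The values below are assumptions, set against the planned difference of 0.39.

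| f(SC) | f(control) | d, both arms | Shift |
|---|---|---|---|
| 0.20 | 0.20 | equal | 0.00 |
| 0.30 | 0.10 | 0.20 to 0.39 | +0.04 to +0.078 |
| 0.10 | 0.30 | 0.20 to 0.39 | −0.04 to −0.078 |
| 0.30 | 0.10 | −0.20 | −0.04 |

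Equal removal does not guarantee zero either. With 0.20 removed from each arm, d(SC) = 0.39 and d(control) = 0, the shift is 0.20 × 0.39 = +0.078. With those d values exchanged it is −0.078. The sign depends on quantities the article does not give.

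**The case against.** The strongest reply is that withdrawal is not exclusion from analysis. Section 4.4 never says withdrawn participants are left out, and section 4.5 sets no analysis population. Analysis sets and missing-data rules commonly sit in an analysis plan or full protocol not shown here. The sentence in section 2.6 may only clarify that unblinding does not cost a participant their place in the analysis, and its wording is unclear enough that reading it as intention-to-treat is itself an interpretation. This stands against any claim that a completer analysis is prescribed. It does not answer the data-collection problem, which lies in a rule that the article does state.

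Three stronger readings are tempting, and the documents do not support them.

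- *Non-adherent participants have no outcomes at months 1 to 3.* Visits before withdrawal take place, and indicators are recorded when the drug is stopped. Only later scheduled values are at risk.
- *The rule favours SC.* Heavier burden in that arm is plausible, but there are no adherence, dropout or outcome data by arm. The article also calls the trial double-blind with blinded participants, so the absence of a placebo powder is itself unclear.
- *The effect is overstated by a known percentage.* If a fraction p of the SC arm leaves with zero benefit and the rest gain 0.39, the overstatement is 1/(1 − p) − 1, or 11%, 25% and 43% at p = 0.1, 0.2 and 0.3. That only restates the zero-benefit assumption. It also treats an overall dropout rate as SC-arm non-adherence, and the pilot's 0.39 as an effect in adherers.

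**Conclusion.** The concern holds as a defect in what the protocol fixes. Non-adherence and failure to persist are grounds for withdrawal, no assessment after withdrawal is stated, and analysis as assigned is mentioned for unblinded participants only. Followed as written, scheduled SDBG and CV values after withdrawal are lost for a group selected on post-randomisation adherence, about 6 per arm if the planned 20% dropout occurs and is equal between arms. The between-group tests therefore risk comparing adherent participants.

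The size of the bias cannot be computed from the article, and its direction is open. It may favour SC if the added powder leads to more withdrawals among poor responders in that arm. Under other equally undocumented assumptions it is zero or runs against SC. The conclusion rests on taking section 4.4 literally and on reading the phrase in section 2.6 as intention-to-treat.

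**What to change.** - **Section 4.4.** State that non-adherence or stopping study treatment does not end follow-up. Collect the remaining month 1, 2 and 3 glucose profiles from everyone who still consents. Record the date of and reason for stopping treatment separately from withdrawal of consent. This concerns data collection only and leaves decisions on stopping treatment as they are.
- **Section 2.6.** Replace the sentence on unblinded participants with: *All randomised participants are analysed in the arm to which they were assigned, whether or not they adhered or were unblinded.* Keep an analysis of adherent completers as a sensitivity analysis only.

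The cost is two changes of wording and continued monthly finger-prick profiles in a few participants, about 6 per arm at 20%. The estimated effect may be smaller than in adherent participants alone. The sample size does not change on this account.
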